## Investigator Responsibilities

By signing the Agreement of Investigator form, the Investigator agrees to:

1. Conduct the study in accordance with the protocol and only make changes after notifying the Sponsor (or designee), except when to protect the safety, rights or welfare of subjects.
2. Personally conduct or supervise the study (or investigation).
3. Ensure that the requirements relating to obtaining informed consent and IRB review and approval meet Chinese guidelines.
4. Report to the Sponsor or designee any AEs that occur in the course of the study, in accordance with the ethics committee of the Second Affiliated Hospital of Chongqing Medical University.
5. Ensure that all associates, colleagues and employees assisting in the conduct of the study are informed about their obligations in meeting the above commitments.
6. Maintain adequate and accurate records in accordance with the ethics committee of the Second Affiliated Hospital of Chongqing Medical University and to make those records available for inspection with the Sponsor (or designee).
7. Ensure that an IRB that complies with the requirements of the ethics committee of the Second Affiliated Hospital of Chongqing Medical University will be responsible for initial and continuing review and approval of the clinical study.
8. Promptly report to the IRB and the Sponsor (or designee) all changes in the research activity and all unanticipated problems involving risks to subjects or others (to include amendments and IND safety reports).
9. Seek IRB approval before any changes are made in the research study, except when necessary to eliminate hazards to the patients/subjects.

APPENDIX 1. Schedule of Study Visits

|  | **Visit 1 (Day/Week/Month #)a** | **Visit 2 (Day/Week/Month #)a** | **Visit 3 (Day/Week/Month #)a** |
| --- | --- | --- | --- |
| Informed Consent | **x** |  |  |
| Medical History | **x** |  |  |
| Complete Physical Exam | **x** |  |  |
| Abbreviated Physical Exam |  | **x** | **x** |
| Height | **x** | **X** | **X** |
| Weight | **x** | **x** | **x** |
| WC |  |  |  |
| FAT% |  |  |  |
| Vital Signs | **x** | **x** | **x** |
| Pharmacokinetics |  | **x** |  |
| Serum Fetuin-B | **x** |  |  |
| Pregnancy Test (Urine or Serum) | **x** |  |  |
| Hematology | **x** |  |  |
| OGTT | **x** |  |  |
| EHC | **x** |  |  |
| Urinalysis | **x** |  |  |
| Dispensing or Administration of Study Drug | **X** | **X** | **X** |
| Counting of Returned Study Drug |  | **X** | **X** |
| Concomitant Medication Review | **X** | **X** | **X** |
| Adverse Experiences |  |  |  |

a 2 days

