| **FDA** | Food and Drug Administration |
| **Fins** | fasting insulin |
| **GCP** | Good Clinical Practice |
| **HIPAA** | Health Insurance Portability and Accountability Act of 1996 |
| **HOMA2-IR** | homeostasis model assessment of insulin resistance |
| **ICF** | informed consent form |
| **ICH** | International Conference on Harmonisation |
| **IEC** | Independent Ethics Committee |
| **IGT** | impaired glucose tolerance |
| **IR** | insulin resistance |
| **IRB** | Institutional Review Board |
| **Lira** | liraglutide |
| **LSD** | Fisher’s Least Significant Difference |
| **OGTT** | oral glucose tolerance test |
| **PI** | Principal Investigator |
| **SAE** | serious adverse experience |
| **WHR** | waist-to-hip ratio |
| **2h-BG** | 2-hour blood glucose post-glucose load |

Protocol Synopsis

| **TITLE** | Association of serum Fetuin-B with insulin resistance and pre-diabetes in young Chinese women: evidence from a cross-sectional study and effect of liraglutide |
| --- | --- |
|  |  |
| **SPONSOR** | [name] |
|  |  |
| **FUNDING ORGANIZATION** | The National Natural Science Foundation of China (No. 81670755), the Natural Science Foundation of Chongqing (No.cstc2017jcyjAX0050) |
| **NUMBER OF SITES** | +86, +023 |
|  |  |
| **RATIONALE** | Fetuin-B has been reported to be involved in glucose and lipid metabolism and associated with the occurrence of diabetes. The main purpose of this study is to explore the changes of circulating Fetuin-B in young women with pre-diabetes and to analyze the relationship between Fetuin-B and the occurrence and development of IR.. |
|  |  |
| **STUDY DESIGN** | This is a cross-sectional study. |
|  |  |
| **PRIMARY OBJECTIVE** | Explore the changes of circulating Fetuin-B in young women with pre-diabetes and to analyze the relationship between Fetuin-B and the occurrence and development of IR |
|  |  |
| **SECONDARY OBJECTIVES** | Explore the effects of liraglutide (Lira) on Fetuin-B and obesity. |
|  |  |
| **NUMBER OF SUBJECTS** | 304 |
|  |  |

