## Secondary Objectives

The secondary objective is to assess the clinical efficacy as measured by the change in physical examination and biochemical tests, OGTT, and EHC tests before treatment, 12 and 24 weeks after treatment.

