# STUDY PROCEDURES AND GUIDELINES

A Schedule of Events representing the required testing procedures to be performed for the duration of the study is diagrammed in Appendix 1.

Prior to conducting any study-related activities, written informed consent and the Health Insurance Portability and Accountability Act (HIPAA) authorization must be signed and dated by the subject or subject’s legal representative. If appropriate, assent must also be obtained prior to conducting any study-related activities.

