### Vital Signs

Physical examination and biochemical tests, OGTT, and EHC tests were performed before treatment, 12 and 24 weeks after treatment.

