## Visit 3 (24 weeks)

1. Record any Adverse Experiences and/or Review subject diary for adverse experiences and dosing compliance.
2. Record changes to concomitant medications.
3. Perform abbreviated physical examination.
4. Perform and record vital signs.
5. Collect blood for clinical laboratory tests (TC, TG, HDL-C, LDL-C, FFA, HbA1c, FBG, 2h-BG, FIns, 2h- INS).
6. List all additional procedures.

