## Analysis of Primary Endpoint

After application of lira, Physical examination and biochemical tests, OGTT, and EHC tests were performed before treatment, 12 and 24 weeks after treatment.

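### Appendix 1 marks Fetuin-B, OGTT and the clamp at baseline only, and the visit lists omit Fetuin-B and the clamp, against narrative sections that repeat the OGTT and clamp at weeks 12 and 24

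*Protocol*

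**What the plan says.** **Objectives.** The synopsis gives the secondary objective as "Explore the effects of liraglutide (Lira) on Fetuin-B and obesity". Section 3.2 words it as "the change in physical examination and biochemical tests, OGTT, and EHC tests before treatment, 12 and 24 weeks after treatment".

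**Narrative timing.** Under Vital Signs, Section 9.1 states "Physical examination and biochemical tests, OGTT, and EHC tests were performed before treatment, 12 and 24 weeks after treatment". The synopsis (Efficacy Evaluations) and Section 15.3 give the same three time points for OGTT and EHC. Section 15.5 repeats both tests at week 12. Under OGTT Test, Section 9.2 has serum Fetuin-B drawn at 0, 30, 60 and 120 minutes of the OGTT.

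**Schedule.** Section 9 says "A Schedule of Events representing the required testing procedures to be performed for the duration of the study is diagrammed in Appendix 1". In Appendix 1 the Fetuin-B row reads "Serum Fetuin-B | x", with Visits 2 and 3 blank. The OGTT and EHC rows have the same pattern. The waist circumference (WC) and Fat % rows carry no mark at any visit.

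**Visit lists.** The blood item at Visit 3 is "Collect blood for clinical laboratory tests (TC, TG, HDL-C, LDL-C, FFA, HbA1c, FBG, 2h-BG, FIns, 2h- INS". Visits 1 and 2 and the Early Withdrawal Visit carry the same item. None of the four lists names Fetuin-B, OGTT or EHC.

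**The concern.** The liraglutide subgroup has no comparator described, so its evidence is each woman's change from her own baseline. That needs a baseline value and at least one follow-up value of each outcome. Fetuin-B is the biomarker in the study title. The clamp M-value (below 6.28) is how the protocol defines insulin resistance. Coordinators usually work from the schedule and the visit lists, and here neither asks for Fetuin-B or a clamp after baseline.

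A sample or clamp missed at week 12 or 24 cannot be recovered later, and Section 12.3 does not replace women who withdraw. Section 2 of the protocol faults earlier work for lacking an intervention, so this subgroup carries weight in the study's argument.

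**Working it through.** The protocol states no sample size, power or alpha figure that bears on this point. The check is a cross-tabulation of each assessment against the three visits (weeks 0, 12 and 24).

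| Assessment | Appendix 1 | Section 10 visit lists | Narrative sections |
| --- | --- | --- | --- |
| Serum Fetuin-B | 1 of 3 (Visit 1) | 0 of 3 | 3 of 3, by inference only |
| OGTT | 1 of 3 (Visit 1) | not named; 2h-BG and 2h-INS at 3 of 3 | 3 of 3, explicit |
| EHC (M-value) | 1 of 3 (Visit 1) | 0 of 3 | 3 of 3, explicit |
| FBG and FIns | no row of their own | 3 of 3 | 3 of 3, within biochemical tests |
| WC and Fat % | 0 of 3 | not named; a physical examination at 3 of 3 | part of the physical examination |

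**Step 1: the inference for Fetuin-B.** No section states outright that Fetuin-B is measured at week 12 or 24. Sections 3.2 and 9.1 do not name it in their timing sentences, and the biochemical list in Section 9.2 does not include it. The route has two links: OGTT is repeated at weeks 12 and 24 (Section 9.1), and Fetuin-B is drawn during the OGTT (Section 9.2). Appendix 1 contradicts both links, because it marks OGTT and Fetuin-B at Visit 1 only.

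**Step 2: what each source yields.** Within-subject change at week *t* is Y(*t*) − Y(0), so the maximum number of follow-up values is women treated × post-baseline visits scheduled. Section 8.1 gives 26 women treated; Section 15.5 planned 30.

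- Appendix 1: 26 × 0 = 0 follow-up values, for Fetuin-B and for the M-value.
- Visit lists: 26 × 0 = 0 for both, and no baseline value is named either.
- Narrative: 26 × 2 = 52 for each (30 × 2 = 60 at the planned size).

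**Step 3: what survives.** FBG and FIns appear in the Visit 1, 2 and 3 lists, and the synopsis lists HOMA2-IR as an evaluation. A site following only the visit lists would still have a fasting index of insulin resistance at all three time points. It would have no M-value and no Fetuin-B.

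**Step 4: WC and Fat %.** Section 9.1 (Physical Examination) includes both. Appendix 1 marks a complete examination at Visit 1 and an abbreviated one at Visits 2 and 3. The content of the abbreviated examination is not defined, so coverage of WC and Fat % at follow-up is unclear.

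**The case against.** The strongest reply is that most of the text already schedules the repeat tests. The synopsis and Sections 3.2, 9.1 and 15.3 agree on three time points for OGTT and EHC, and a repeat OGTT brings Fetuin-B with it. The schedule also looks like an unfinished template. Its column heads still hold day/week/month placeholders. Its Adverse Experiences row is blank although the text requires adverse events to be recorded. The lists for Visits 1 to 3 end with an unfilled line for additional procedures. The Visit 1 list omits EHC even though Section 9.2 has it performed in every subject. The omissions are therefore weak evidence of a decision to measure only at baseline.

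That stands as an explanation, and it rules out three stronger readings that a reader might infer:

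- That the liraglutide effect cannot be estimated at all. This holds only if Appendix 1 or the visit lists override the narrative.
- That insulin resistance goes unmeasured after treatment. HOMA2-IR remains available from the visit lists.
- That WC and Fat % are never measured. They belong to the physical examination.

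It does not remove the problem. Section 9 gives Appendix 1 its governing status, nothing says which text prevails, and the link to follow-up Fetuin-B is never stated. The blank cells are also selective: Height, Weight and Vital Signs in the same table are marked at all three visits.

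**Conclusion.** The protocol contradicts itself on when its main liraglutide outcomes are measured. This is an internal inconsistency, not a design choice. Post-baseline Fetuin-B and clamp assessments are 0 of 2 visits in Appendix 1 and 0 of 2 in the visit lists. The narrative has 2 of 2, explicit for the clamp and inferred for Fetuin-B.

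The consequence is conditional. If sites follow the schedule or the visit lists, change in Fetuin-B and in the M-value has no follow-up data; if they follow the narrative, it does. The protocol does not settle which was done. It warrants correction because the lost values would be the subgroup's key outcomes and could not be recovered.

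**What to change.** - In Appendix 1, mark Serum Fetuin-B, OGTT, EHC, WC and Fat % at Visits 1, 2 and 3, and fill in the visit timing in the column heads.
- Add the same items to the lists in Sections 10.1, 10.2 and 10.3 and, where feasible, to the Early Withdrawal Visit.
- State in Section 3.2 or 9.2 that serum Fetuin-B is measured at weeks 12 and 24 in the liraglutide subgroup.
- Define the abbreviated physical examination, or list WC and Fat % separately from it.

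Which of the four OGTT time points supplies the Fetuin-B value for the change analysis can be left to the SAP.

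The cost is wording in the protocol and schedule. The narrative already commits to the repeat OGTT and EHC, and Section 9.2 already draws Fetuin-B during the OGTT, so no new procedure is added.

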## Interim Analysis

All of the subjects were asked to come back to the outpatient to receive physical examination and biochemical tests, OGTT, and EHC tests at 12 week to assess the effect of lira.

The sample size for this protocol was determined by the patients number of the Second Affiliated Hospital of Chongqing Medical University from January 2017 to December 2019. We planed to enroll 300 subjects for cross-sectional study and 30 subjects for lira administration.

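### Appendix 1 marks Fetuin-B, OGTT and clamp at Visit 1 only and the visit lists name none of them, contrary to the text; if followed, change in Fetuin-B and M-value under liraglutide could not be estimated

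*Protocol*

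**What the plan says.** **The text.** The synopsis gives as a secondary objective: "Explore the effects of liraglutide (Lira) on Fetuin-B and obesity". Its efficacy evaluations and Section 9.1 (Vital Signs) state: "Physical examination and biochemical tests, OGTT, and EHC tests were performed before treatment, 12 and 24 weeks after treatment". Section 3.2 measures efficacy by change in, among other things, "OGTT, and EHC tests before treatment, 12 and 24 weeks after treatment". Section 15.3, on the primary endpoint, has "OGTT, and EHC tests were performed before treatment, 12 and 24 weeks after treatment", and Section 15.5 has "OGTT, and EHC tests at 12 week to assess the effect of lira". Section 4.1 puts the subgroup's evaluations at the same three times. Section 9.2 (OGTT Test) takes Fetuin-B samples at 0, 30, 60 and 120 minutes of the OGTT.

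**The schedule.** Section 9 opens: "A Schedule of Events representing the required testing procedures to be performed for the duration of the study is diagrammed in Appendix 1". In that appendix the Fetuin-B row is "Serum Fetuin-B | x", and nothing follows under Visits 2 and 3. The OGTT and EHC rows are marked in the same way.

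**The visit lists.** Sections 10.1, 10.2 and 10.3 carry the same blood-test item: "Collect blood for clinical laboratory tests (TC, TG, HDL-C, LDL-C, FFA, HbA1c, FBG, 2h-BG, FIns, 2h- INS". None of the three lists names Fetuin-B, OGTT or EHC.

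**The concern.** The treated subgroup exists to show what liraglutide does to Fetuin-B and to insulin resistance. Section 2 justifies the study partly by the lack of an intervention experiment linking the two. The M-value from the clamp is the protocol's own criterion for insulin resistance (synopsis and Section 6.2).

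Change from baseline needs a baseline value and a later value. The two parts of the protocol that staff would work from, the schedule table and the visit lists, order no later value of either variable. No analysis plan can recover samples and clamps that were not taken.

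Fetuin-B is the more exposed of the two. No passage directly orders it at week 12 or week 24. It reaches those visits only through the OGTT draws, so dropping the OGTT there also drops Fetuin-B.

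**Working it through.** The protocol gives no figure to reproduce here. The check sets the three sources side by side, for weeks 0 / 12 / 24.

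| Assessment | Narrative text | Appendix 1 | Lists in 10.1 / 10.2 / 10.3 |
|---|---|---|---|
| OGTT | yes / yes / yes | yes / no / no | not named |
| EHC (M-value) | yes / yes / yes | yes / no / no | not named |
| Serum Fetuin-B | yes / implied / implied | yes / no / no | not named |
| FBG, FIns | yes / yes / yes, as biochemical tests | no row | yes / yes / yes |
| 2h-BG, 2h-INS | yes / yes / yes, as biochemical tests | no row | yes / yes / yes |

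*Step 1, cells for the first three rows.* The text asks for 3 assessments x 3 visits = 9. Appendix 1 marks 3 of 9, all at Visit 1. The visit lists name 0 of 9. The shortfall in Appendix 1 is 9 - 3 = 6 cells.

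*Step 2, values lost if the table and lists are followed.* Section 8.1 gives 26 treated women, and Section 15.5 planned 30. With two post-baseline visits and one value counted per woman per visit:
- expected from the text: 26 x 2 = 52, or 30 x 2 = 60, for Fetuin-B and likewise for the M-value;
- ordered by Appendix 1 and the lists: 26 x 0 = 0, or 30 x 0 = 0.

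*Step 3, what survives.* The visit lists collect FBG and FIns at weeks 12 and 24. These are the inputs to HOMA2-IR, which the synopsis lists among its other evaluations. The lists also collect 2h-BG and 2h-INS. The abbreviation list defines 2h-BG as a value after a glucose load, although Section 9.2 calls both postprandial. On the first definition, Visits 2 and 3 need a glucose load that Appendix 1 does not schedule, which is a further mismatch. The 30- and 60-minute OGTT samples would not be covered.

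*Step 4, could this be a reading error in the table?* Unlikely. In the same table Weight, Vital Signs, drug administration and concomitant medication carry marks under all three visits, so the columns were kept.

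**The case against.** The strongest reply is that the text does provide for these measurements. The synopsis and Sections 3.2, 9.1 and 15.3 all place OGTT and clamp at weeks 12 and 24, and several of them say the tests were performed. Nothing gives the table precedence over the text. The table is visibly unfinished: its visit headings still hold placeholders, and the rows for waist circumference, body fat and adverse experiences are blank at every visit. The visit lists are weak evidence of intent, because the Visit 1 list also omits tests that the text requires of every woman at baseline. All of this stands. It makes the defect a contradiction between parts of one document, not an absence. It does not remove the defect, since Section 9 points staff to the table for what is required. The line in Sections 10.2 and 10.3 calling for additional procedures is unfilled template wording and names none.

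One might also say that the Visit 1 marks describe only the cross-sectional cohort. That does not fit, because the same table has study drug given at all three visits.

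A reader might infer more than the documents support:
- *That no effect on insulin resistance could be measured.* HOMA2-IR would remain available; the clamp M-value is what is lost.
- *That no glucose-load data exist after baseline.* The 2-hour glucose and insulin values are in the visit lists.
- *That the text expressly orders Fetuin-B at weeks 12 and 24.* It does so only by implication, through the objective and the OGTT sampling.
- *That the missing Fetuin-B sample at Early Withdrawal is part of the contradiction.* No passage calls for it there.

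**Conclusion.** The point holds as an internal contradiction that must be reconciled. If Appendix 1 and the visit lists are followed, change in Fetuin-B and change in M-value under liraglutide cannot be estimated: 0 of 52 post-baseline values for each with 26 women, 0 of 60 with 30. If the narrative text is followed, both can be.

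The counts assume that every treated woman attends both later visits; Section 8 says that 26 were followed to the end. They describe what the documents order. The documents do not show what sites did.

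The primary objective, the association of Fetuin-B with insulin resistance and impaired glucose tolerance, is not affected, because all three assessments are marked at Visit 1. The exposure is confined to the liraglutide subgroup. There it reaches both the secondary objective and Section 15.3, which rests on the same OGTT and clamp measurements.

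**What to change.** Bring Appendix 1 and Sections 10.1 to 10.3 into line with the text.

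1. In Appendix 1, mark Serum Fetuin-B, OGTT and EHC at Visits 1, 2 and 3 for the liraglutide subgroup. This adds six cells. Say that women in the cross-sectional part alone have these tests at Visit 1 only.
2. Name the three assessments in each of the lists in Sections 10.1, 10.2 and 10.3.
3. State explicitly that Fetuin-B is measured at weeks 12 and 24, so that it no longer depends on inference from the OGTT sampling.

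The cost is wording. The repeat OGTT and clamp are already in the text, and Fetuin-B comes from blood drawn during the OGTT. If the visits are already complete, rewording cannot create data; the report should then state how many of the 52 (or 60) post-baseline values exist for each variable.

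Adding Fetuin-B to the blood draw at Early Withdrawal (Section 10.6) is optional. It is a new request and not part of this reconciliation.
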